**Peripheral nervous system**	
Guillain-Barré Syndrome (30)	Inflammatory immune-mediated polyradiculoneuropathy with acute onset that manifests with tingling, progressive weakness, autonomic disfunction and pain.
Critical illness myopathy/neuropathy (31)	Neuromuscular weakness in the intensive care setting.
Hypogeusia/hyposmia (32)	Quantitative disorders characterized by reduction of taste or smell.
**Others**	
Hypoxic-ischemic brain injury (33)	Reduction in blood supply, oxygen supply or utilization that determines a decreased oxygen delivery to the brain and post cardiac arrest hypoxic ischemic brain injury (reduction in blood supply, oxygen supply or utilization that determines a decreased oxygen delivery to the brain due to cardiac arrest).

### Statistical Analysis Plan

Planned analyses will comprise of descriptive summaries and regression-based methods for estimating associations between patient-level variables, neurological complications, and outcomes. Descriptive statistics for summarizing the study cohort will be presented as medians with interquartile ranges and frequencies with percentages for continuous and categorical variables, respectively. As an observational study, missing data are expected; a data completeness summary will accompany descriptive summaries for all variables considered. The incidence of neurological complications will be calculated as the number of events per 1,000 ICU days and as the number of events divided by the total number of ICU admissions. Incidence will be estimated per complication using logistic and Poisson regression; Poisson models will include patient days as an offset to account for varying ICU exposure. Baseline models will be adjusted for patient-level variables (e.g., sex, age, country) and calendar time to account for the timing of different COVID-19 waves. Additional covariates will be informed by univariate analysis and penalized regression techniques to address the secondary objective related to incidence.

Analysis of associations between neurological complications and clinical outcomes will be examined using generalized linear mixed models for binary outcomes and parametric survival models for time-to-event outcomes. Evidence of potential associations, including patient demographics and clinical signs assessed during ICU admission, will initially be assessed using univariate analysis. Results of univariate analysis will be used to inform variable selection for multivariable analysis.

Multivariable models for all study objectives will be adjusted for known confounders as fixed or random effects, including study center, country, and calendar time. Model results will be presented as odds ratios (binary outcomes), relative risks (count outcomes) or hazard ratios (time-to-event outcomes) with 95% confidence intervals and *p*-values from hypothesis tests as appropriate.

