### Objectives

The primary objective is to identify and describe the type and incidence of neurological complications in COVID-19 patients before and after admission to ICU, for all ICU patients selected patient subgroups (sex, age, country, treatment, COVID-19 wave).

Secondary objectives include: To evaluate the effect of neurological complications on outcomes after COVID-19, i.e., mortality, duration of ICU and hospital stay, neurological outcome (modified Rankin scale, mRS) at discharge, incidence of delirium and cognitive outcome at discharge. To identify factors related to the occurrence of neurological complications (including neurological injury due to the antiviral therapy).

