In the latest 2 years, knowledge has increased regarding extra-pulmonary complications of COVID-19 and their effect on outcome. Severe COVID-19 disease potentially involves multiple organs, including pulmonary, coagulation, cardiac, neurological, renal, hepatic, and gastrointestinal manifestations (34). Many neurological manifestations have been described recently in small observational studies, but additional evidence is needed from large multicentric cohorts. For this reason, in the present study we aim to depict the incidence, risk factors, and impact on outcome of neurological complications in critically ill COVID-19 patients from a large observational multicentric cohort. Data regarding pre-admission neurological manifestations, in-hospital neurological complications as well as ICU-and-hospital length of stay, neurological outcome (mRS), and mortality are available in the eCRF. This sub-analysis of the COVID-19 Critical Care Consortium Observational Study was pre-planned during the first/second wave of the pandemic (late 2020), thus increasing the data quality and minimizing the chance of spurious results and limiting the potential of exploratory learning. The number of patients included in the main study is continuously growing since the beginning of pandemic, allowing to obtain a large sample size, which can provide important information on the current incidence and characteristics of neurological manifestations in COVID-19 patients, evaluating potential associations between predictors and development of neurological complications, and assessing outcomes at discharge from ICU and from hospital and 28-days patients' outcomes. The included patients will be from different countries and centers, including low incoming countries. The patients will be also included during different waves and years of the pandemic, before and after the advent of vaccination campaigns, and with different variants of COVID-19 (i.e., omicron, delta, etc.). This will provide interesting insights on the differences in epidemiology, management strategies, geographical, and economical characteristics of COVID-19 adult patients who manifest neurological complications admitted to ICU. This global research context will provide the lens through which the study as well as its methodological approaches, findings, conclusions, and recommendations can be viewed.

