### Incidence and Types of Neurological Manifestations and Complications of COVID-19

The importance of investigating neurological manifestations in COVID-19, assessing their risk factors, and association with outcome is justified by the increasing identification in the available literature of many studies which reported high morbidity and mortality and poor neurological outcome in COVID-19 patients who manifest neurological complications, with the need for identifying and investigating such alterations in a bigger cohort of COVID-19 critically ill patients. Indeed, regarding each of the identified neurological manifestations of COVID-19, the data are fragmentary and come from different small cohorts. Myalgia, dysgeusia, and taste dysfunction were frequently reported (33% of cases), altered mental status in 32%, headache 29%, encephalopathy 26%, alteration of consciousness 13%, stroke 12%, dizziness 10%, vision impairment 6%, intracerebral hemorrhage, 5%, seizure 4%, encephalitis 2%, and GBS 1% (35). Intracranial hemorrhage was identified in 477 patients with a prevalence of 0.85% and a mortality of 52% suggesting a very poor prognosis despite rare incidence (36). The prevalence of intracranial hemorrhage, ischemic stroke, and hypoxic ischemic brain injury was higher in patients with COVID-19 who underwent ECMO support (5.9%) with a mortality of 92% (17). Acute disseminated encephalomyelitis and acute hemorrhagic leukoencephalitis have been reported in 46 patients with COVID-19 only, of whom 32% died (37).

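### Risk factors for neurological complications are selected from the data and then reported with 95% intervals and p-values, with no described allowance for the selection; the effect may be substantial or negligible depending on inputs the article does not state

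*Protocol article*

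**What the plan says.** The protocol article's Objectives section lists as a secondary objective: "To identify factors related to the occurrence of neurological complications". In the Statistical Analysis Plan section, baseline models adjust for patient-level variables (sex, age and country are the examples) and calendar time. Beyond that set: "Additional covariates will be informed by univariate analysis and penalized regression techniques to address the secondary objective related to incidence". For the models linking complications to clinical outcomes, the pattern is similar: "Results of univariate analysis will be used to inform variable selection for multivariable analysis".

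The reporting format covers all objectives: "Model results will be presented as odds ratios (binary outcomes), relative risks (count outcomes) or hazard ratios (time-to-event outcomes) with 95% confidence intervals", together with p-"values from hypothesis tests as appropriate".

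The section describes no validation sample, resampling of the selection, correction for selection or exploratory label. The Discussion instead credits the planning of the sub-analysis in late 2020 with keeping spurious findings down and restricting data-led exploration.

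**The concern.** When the aim is to identify factors, the selected coefficients are the result, not background adjustment. A factor enters because its estimate was large in this sample. A standard interval computed afterwards on the same sample treats the factor as if it had been chosen beforehand. Three consequences can follow:

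- coverage for selected factors can drop below the stated 95%;
- weak effects that survive selection are overstated;
- falsely significant noise factors form a larger share of a shorter list.

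Pre-planning the sub-analysis protects against this only for what is fixed in advance, and the added covariates are left to the data. Readers would take the printed intervals at face value, although the planned procedure does not secure their nominal level.

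**Working it through.** **Inputs from the article.** Selection is by univariate analysis and penalized regression, and intervals are at 95%. Event rates cited in the Discussion ("stroke 12%, dizziness 10%, vision impairment 6%, intracerebral hemorrhage, 5%, seizure 4%, encephalitis 2%, and GBS 1"%) were used only to set a simulated range of 2% to 12%. The article gives no error-rate figure to reproduce.

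**Assumptions.** The sample size is not stated ("The number of patients included in the main study is continuously growing since the beginning of pandemic"), so 2,000, 4,000 and 5,000 were used. Also assumed: a two-sided 0.05 test, the screening thresholds, 30 candidates, the effect sizes, and an ordinary refit on the same data.

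**Analytic check.** For an independent noise factor that passes a screen at p<s and is refitted on the same data, P(p<0.05 | kept) ≈ 0.05/s, and coverage ≈ 1 − 0.05/s:

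- s = 0.20: 1 − 0.25 = 0.75
- s = 0.10: 1 − 0.50 = 0.50
- s = 0.05: 1 − 1 = 0

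**Simulation, independent candidates.** Each data set had 2 factors with OR 1.5, 3 with OR 1.15 and 25 noise factors, with a logistic refit after selection. There were 150 data sets per setting, or 60 for the lasso. Results for n = 2,000 and 5% events:

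| Selection | Factors kept | Coverage, all kept | Coverage, kept noise | Falsely significant noise factors | As share of kept | Weak log-OR, estimate/true |
|---|---|---|---|---|---|---|
| None (all 30) | 30 | 0.95 | 0.96 | 1.05 | 1.05/30 = 3.5% | 1.06 |
| p<0.05 | 4.00 | 0.69 | 0.16 | 1.09 | 1.09/4.00 = 27% | 1.83 |
| p<0.10 | 5.43 | 0.74 | 0.45 | 1.29 | 1.29/5.43 = 24% | 1.65 |
| p<0.20 | 8.92 | 0.82 | 0.72 | 1.47 | 1.47/8.92 = 16% | 1.46 |
| Cross-validated lasso | 8.86 | 0.82 | 0.74 | 1.38 | 1.38/8.86 = 16% | 1.55 |

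Coverage over all kept factors is the average weighted by the number kept. At p<0.05, for example, this is (1.96×0.952 + 0.74×0.910 + 1.30×0.164)/4.00 = 0.69.

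Across the settings (n = 2,000 with 5% or 12% events, n = 5,000 with 2%; lasso only at n = 2,000):

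- Coverage for kept noise factors was 0.11–0.23 (p<0.05), 0.45–0.52 (p<0.10), 0.72–0.79 (p<0.20) and 0.74–0.80 (lasso).
- Selected weak effects were overstated 1.2 to 1.8 fold on the log-OR scale, although their intervals still covered in 0.91–0.98 of cases.
- Factors with OR 1.5 kept coverage of 0.93–0.98.

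A second run (n = 4,000, 5% events, 30 candidates) gave 0.02–0.14, 0.52 and 0.76–0.79 for kept noise factors at the three screens. With real effects included, coverage over all kept factors was 0.77–0.87.

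**Simulation, correlated candidates.** With real effects and correlation 0.1 or 0.3, coverage in the n = 4,000 run was 0.94–0.98. At n = 2,000, correlation 0.3 and p<0.10, the screen kept 24.65 of the 25 noise factors and their coverage was 0.955. Candidates correlated with a true factor are associated with the outcome one at a time, so they pass the screen and little selection takes place. With correlation 0.3 and no real effects, coverage was 83–85%, 80–81% and 59–65% at screens of 0.20, 0.10 and 0.05. The lasso was not run with correlated candidates.

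**Is the false-positive count caused by screening?** With K noise candidates and no selection, P(at least one p<0.05) = 1 − 0.95^K, which is 64% for K = 20 and 79% for K = 30. At n = 4,000 with 30 candidates the simulated figure was 0.79 for the unselected model and 0.76–0.79 after screening. The mean number of falsely significant noise factors was about 1.0–1.3 without selection and 1.0–1.5 with it.

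**The case against.** The strongest reply is that the article does not say selected factors are refitted without penalty on the same data, or how intervals are formed after penalization. It says covariates are informed by these techniques and that p-values are given as appropriate. Thresholds, penalty, candidate list and internal validation are details that a condensed article may leave to a full plan. This stands in part: those gaps are not counted as faults here, and standard intervals from the same data remain a condition of the point. What the article does state is the combination of outcome-driven selection with 95% intervals and p-values.

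The second reply also stands: ICU severity scores, comorbidities and laboratory values are plausibly correlated (an assumption), and the article itself cites several independent predictors. Under those conditions coverage was near 95%.

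A reader might be tempted by three stronger readings that the documents do not support:

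- That the intervals for the risk-factor list definitely lack 95% coverage. This depends on unstated inputs, and strong factors and the forced baseline covariates are little affected.
- That screening causes a 64–79% chance of at least one false factor. That chance arises from the number of candidates and is nearly the same with no selection.
- That the search is repeated for each of the 10 rows of Table 1. The sentence "Incidence will be estimated per complication using logistic and Poisson regression" concerns incidence estimation, and the risk-factor objective refers to complications collectively. Repetition is only an inference.

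The article also speaks of associations and concedes bias, confounding and no claim of causality. That limits interpretation but does not correct the intervals.

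**Conclusion.** The point holds as a conditional one and merits a change of moderate priority. The stated procedure describes nothing that makes the intervals allow for the search, and the Discussion's reassurance about spurious results does not extend to factors chosen from the data.

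The size cannot be pinned down from the article. The shortfall, from 95% to roughly 0.77–0.87 over all kept factors at n = 4,000 (0.69–0.82 at n = 2,000 with 5% events), is a worst-case type of result that rests on independent candidates and a same-data refit. The other end is almost no loss, with correlated candidates and real effects. Overstatement of weak selected effects was seen with independent candidates; in the one correlated setting where it was reported, it was absent (estimate/true 0.98).

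**What to change.** - Drop the univariate screen as a gate to the multivariable model.
- Fix a candidate list before complications are related to covariates. Include the predictors cited in the Discussion's risk-factor section, such as age, headache at presentation, pre-existing neurological disease, invasive ventilation and neutrophil/lymphocyte ratio. Report these with ordinary 95% intervals. In the independent-candidate simulations the unselected 30-factor model had noise-factor coverage of 0.95–0.96. About 1.0–1.3 noise factors were still significant, because fixing the list does not remove multiplicity.
- For any further factors chosen from the data, repeat the whole selection in bootstrap samples drawn by centre. Report selection frequencies, shrunken estimates and bootstrap intervals, omit naive p-values, and label these factors hypothesis-generating. The coverage of such bootstrap intervals was not simulated here.
- Do not require splitting the data by country. With an assumed 4,000 patients, 1% and 2% incidence give 4,000×0.01 = 40 and 4,000×0.02 = 80 events; halving leaves 20 to 40, too few to select among 20 to 30 candidates.

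The cost is more computation, some rewording, and wider intervals for selected factors. No new data are needed.

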### Data Collection

Data collection started from the commencement of COVID-19 pandemic and is planned to continue until completion of COVID-19 pandemic, as judged by the World Health Organization. According to the COVID-19 Critical Care Consortium Observational Study protocol (21) and neurological sub-study protocol, the following data will be collected: general patient characteristics, age, gender, body mass index (BMI), country, previous chronic comorbidities, scores of severity; premorbid scores [modified Rankin scale (0–6 points), Figure 1; new neurological complications, laboratory findings, imaging, and management of neurological complications (Supplementary Item 2); patient outcome (mortality at discharge, at 28-days, withdrawal of life-saving therapy and reason; mRS at ICU discharge, mRS at 28 days after discharge). Main eCRF of the COVID-19 critical care consortium study and neuro sub-study are provided in the Supplementary Items 3, 4.

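### The outcome models do not account for when in-ICU neurological complications start, so ever/never coding would put immortal-time bias into the survival, length-of-stay and 28-day mortality results

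*Protocol article*

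**What the plan says.** Under Objectives, the primary objective is to "identify and describe the type and incidence of neurological complications in COVID-19 patients before and after admission to ICU", so the complications studied include some that begin during the ICU stay. The first secondary objective listed is "To evaluate the effect of neurological complications on outcomes after COVID-19, i.e., mortality, duration of ICU and hospital stay", followed by neurological and cognitive outcomes. Table 1 includes critical illness myopathy/neuropathy, which it defines as "Neuromuscular weakness in the intensive care setting"; this complication is tied to the stay itself.

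Under Data Collection, mortality is recorded at two points: "patient outcome (mortality at discharge, at 28-days".

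The Statistical Analysis Plan section gives the model classes for this objective: "Analysis of associations between neurological complications and clinical outcomes will be examined using generalized linear mixed models for binary outcomes and parametric survival models", the latter for time-to-event outcomes. On reporting: "Model results will be presented as odds ratios (binary outcomes), relative risks (count outcomes) or hazard ratios (time-to-event outcomes". Adjustment is for known confounders, including center, country and calendar time. For incidence, the same section does deal with time at risk: "Poisson models will include patient days as an offset to account for varying ICU exposure". It gives no counterpart for the outcome models: no time-dependent covariate, landmark or multistate structure. The limitations text concedes bias and confounding only in general terms.

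**The concern.** A patient can have an in-ICU complication only after surviving, and staying in the ICU, long enough to have it. If that patient is classed as exposed from ICU admission, the event-free days before onset are credited to the exposed group. This lowers the apparent death and discharge hazards of complicated patients. Long stay also creates the opportunity for a complication, so complication and stay are associated even when neither affects the other.

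The offset in the incidence models shows that the authors recognise that longer stay gives more opportunity. The same fact affects the outcome models, where stay both drives the exposure and is an outcome. Adjusting for center, country and calendar time does not remove it. At stake is the direction of the mortality and length-of-stay results: a harmful complication could appear protective, and a harmless one could appear to prolong stay.

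**Working it through.** The article gives no hazards, onset times, event counts or sample size on this point, so it has no figure to reproduce. All rates below are assumptions chosen to show the size of the effect.

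**Set-up.** Constant daily hazards in the ICU: complication `c`, death `d`, live discharge `g`, with `s = d + g`. The complication has no effect on death or discharge. Exposure is coded ever/never from ICU admission.

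**Closed form.**
- Mean stay, never complicated: `1/(s+c)`.
- Mean stay, ever complicated: `1/(s+c) + 1/s` (time to onset plus the remaining stay).
- Ratio of mean stays: `2 + c/s`.
- The proportion dying in the ICU is `d/s` in both groups, so the ratio of death rates (the fixed-coded hazard ratio) is the inverse: `s/(2s + c)`.

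**Base case:** `c = 0.01`, `d = 0.02`, `g = 0.05`, so `s = 0.07`.
- Never complicated: `1/0.08 = 12.5` days.
- Ever complicated: `12.5 + 1/0.07 = 26.8` days; ratio 2.14.
- Fixed-coded death hazard ratio: `0.07/0.15 = 0.47`. The true value is 1, and simulation with the complication as a time-dependent exposure returns 1.00.

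**Wider set of assumptions.** Mean ICU stay 10, 15 or 20 days; ICU mortality 40%; 5%, 15% or 30% of patients complicated; post-discharge death hazard 0.001 per day; 1,000,000 simulated patients per scenario.

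| Quantity | Coding | True HR 1 | True HR 2 |
|---|---|---|---|
| Death HR | ever/never | 0.41 to 0.49 | 0.71 to 0.82 |
| Death HR | time-dependent | 0.99 to 1.01 | 1.99 to 2.01 |
| Ratio of mean ICU stays | ever/never | 2.05 to 2.43 | 1.74 to 2.03 |
| 28-day mortality OR | ever/never | 0.44 to 0.77 | 0.88 to 1.62 |
| OR, death by ICU discharge | ever/never | 0.99 to 1.01 | 1.97 to 2.01 |

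With a true hazard ratio of 2, fixed coding puts the estimate below 1, so the direction reverses.

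**How far this depends on onset timing.** Under constant hazards the fixed-coded hazard ratio is always below 0.5, so varying the rates does not test the result properly. Onset timing does. With `d = 0.02`, `g = 0.05`, no true effect, and onset confined to early ICU days:
- First 3 days (12.6% complicated): stay 15.7 against 14.1 days; hazard ratio `14.1/15.7 = 0.90`.
- First 7 days (10.3% complicated): stay 17.4 against 13.9 days; hazard ratio `13.9/17.4 = 0.80`.

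In both cases the 28-day odds ratio is above 0.9.

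**28-day odds ratio in the base case.** It is about 0.73 if only onsets up to day 28 count as exposed, and about 0.63 if onset at any time in the stay counts. This figure depends on counting rules as well as on the hazards.

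**The case against.** The strongest reply is that the article never says complications are coded ever/never. It names model families only, and parametric survival models accept time-dependent covariates. The article is a condensed account, no separate analysis plan is at hand, and covariate coding is often left to such a plan. This stands to the extent that the bias is a consequence of one reading, not something the text prescribes. It does not dispose of the point. A mixed model for a per-patient binary outcome ordinarily carries one exposure value per patient, and the section settles ICU time for incidence while leaving it out where it can determine the direction of the result.

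A second reply is that the largest figures assume onset spread over the whole stay. This also stands: with early onset the bias is much smaller, and the article gives no onset times.

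A third is scope. Complications present at ICU admission carry no immortal time when admission is time zero. The odds ratio for death by ICU discharge was close to its true value under constant hazards. Both limits are accepted.

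A reader might also extend the argument to the incidence analyses in "selected patient subgroups (sex, age, country, treatment, COVID-19 wave", supposing that days and events before treatment start are credited to treated patients. The documents do not support that. Treatment appears there only as a subgroup for describing incidence, the treatments meant are not named, and nothing is said about how days before treatment are assigned.

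**Conclusion.** The point holds in a limited form. The objective covers complications that start in the ICU, and the models named for it make no allowance for onset time. Under ever/never coding from admission, the survival hazard ratio, length-of-stay and 28-day mortality results carry immortal-time bias. With no true effect, the fixed-coded death hazard ratio lies between about 0.4 and 0.9: about 0.4 to 0.5, with stay about doubled, under constant hazards, and about 0.8 to 0.9 if onset falls in the first 3 to 7 days. These sizes rest on assumed hazards and onset patterns.

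A reader might infer that the plan commits to fixed coding, that the bias is certain, or that every mortality result is compromised. The text supports none of these: the coding is unstated, admission complications are unaffected, and death by discharge need not be biased. Nor does the article rank this objective above the other secondary ones; it only lists it first.

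**What to change.** In the Statistical Analysis Plan section, state that:
- for time-to-event and length-of-stay outcomes, complications starting in the ICU enter as a time-dependent covariate, with follow-up split at onset, or through a multistate model with ICU, complication, discharge and death as states;
- for 28-day binary outcomes, a landmark analysis is used: exposure is complications up to a fixed ICU day, among patients still in the ICU on that day;
- complications present at ICU admission are a separate baseline exposure.

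The cost is wording and extra programming. The change relies on onset dates, assumed to be in the eCRF; where dates are missing, exposure can be restricted to complications known to be present by the landmark. The landmark excludes patients who have already left the ICU, a loss that stays small only if the day is early. Under the base-case hazards it is `1 - exp(-0.07 × 3) = 19%` at day 3 and `1 - exp(-0.07 × 7) = 39%` at day 7. These changes remove the immortal-time bias but not confounding by severity of illness.

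### The outcome models do not tie ICU-onset complications to their onset time; if coded ever/never, the death hazard ratio, length-of-stay association and 28-day odds ratio carry immortal-time bias

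*Protocol article*

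**What the plan says.** All references are to the protocol article.

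- **Objectives.** The first secondary objective is "To evaluate the effect of neurological complications on outcomes after COVID-19, i.e., mortality, duration of ICU and hospital stay", together with neurological and cognitive outcomes. The primary objective covers "neurological complications in COVID-19 patients before and after admission to ICU", so complications may be present at ICU day 0 or begin during the stay.
- **Table 1.** At least one complication arises in the ICU by definition: critical illness myopathy/neuropathy, given as "Neuromuscular weakness in the intensive care setting". Stroke, haemorrhage, seizures and delirium can also begin there.
- **Data Collection.** The exposure item is "new neurological complications, laboratory findings, imaging, and management of neurological complications (Supplementary Item 2". The article text does not mention onset dates, and the case report forms are in supplements not shown. Death is recorded as "patient outcome (mortality at discharge, at 28-days, withdrawal of life-saving therapy and reason".
- **Statistical Analysis Plan, outcome models.** "Analysis of associations between neurological complications and clinical outcomes will be examined using generalized linear mixed models for binary outcomes and parametric survival models". The survival models serve the time-to-event outcomes. The section gives adjustment variables and effect measures. It gives no time origin and does not say how a complication enters these models.
- **Statistical Analysis Plan, incidence models.** Here time at risk is handled: "Poisson models will include patient days as an offset to account for varying ICU exposure".

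**The concern.** For an ICU-onset complication, exposure status is unknown at admission and is learned during the same follow-up that supplies the outcome. A patient must stay alive and in ICU until onset to be classed as exposed, while one who dies or leaves early is classed as unexposed. If one row per patient with an ever/never indicator is fitted, the time before onset is counted as exposed survival. For length of stay the direction of dependence is also reversed, because a longer stay gives more opportunity for a complication.

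The listed adjustment variables (centre, country, calendar time) do not remove this, since it persists under perfect confounder control. Nor does the general caveat about bias and confounding under Potential Pitfalls. A larger cohort only makes the wrong estimate more precise. At stake is the first secondary objective: a harmful complication could look neutral or protective for the death hazard, and a harmless one could seem to prolong the stay.

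**Working it through.** The article gives no event counts, hazards or sample size, so there is no figure of its own to reproduce. **Every hazard below is an assumption.**

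**1. Closed form, no true effect.** Let L be the constant daily hazard of leaving ICU (death d plus live discharge) and c the constant daily onset hazard from ICU day 0.

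- The time to the first of onset or exit has mean 1/(L + c), whichever comes first.
- Mean stay without a complication: 1/(L + c).
- Mean stay with a complication: 1/(L + c) + 1/L.
- Ratio of mean stays: 1 + (L + c)/L = 2 + c/L.
- The same fraction d/L dies in both groups, so the ever/never exponential death hazard ratio is the inverse: 1/(2 + c/L).

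| L per day | c per day | Stay ratio | Naive HR |
|---|---|---|---|
| 0.06 | 0.001 | 2.02 | 0.50 |
| 0.06 | 0.02 | 2.33 | 0.43 |
| 1/10 | 0.005 | 2.05 | 0.49 |
| 1/15 | 0.02 | 2.30 | 0.43 |
| 1/15 | 0.05 | 2.75 (simulated about 2.7) | 0.36 |

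**2. Simulation, 1,000,000 patients per scenario.** Onset hazard 0.001, 0.005 or 0.02; death/discharge hazards 0.02/0.04, 0.03/0.04 or 0.015/0.06. Ever/never coding, with live discharge ending follow-up.

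| Quantity | True HR 1 | True HR 2 |
|---|---|---|
| Naive death HR | 0.43-0.50 | 0.73-0.89 |
| 28-day ICU death OR (discharged alive counted as alive) | 0.67-0.77 | 1.43-1.61 |
| Death before ICU discharge OR | 0.99-1.01 | 1.98-2.02 |
| Time-updated death HR | 0.99-1.02 | 2.00-2.02 |

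With no true effect, one scenario (onset 0.001, death/discharge 0.02/0.04) gives mean stays of 33.1 days with and 16.4 days without a complication. A second set with no true effect (mean stay 10-15 days, onset 0.005-0.05 per day, 35% dying) gave naive HR 0.36-0.49 and 28-day OR 0.58-0.80.

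**3. Why death before discharge differs.** Under constant hazards a patient still in ICU dies there with probability d/L, however long the stay so far. Surviving to onset therefore carries no information about the final outcome, and the OR is 1. At a fixed 28 days it does carry information, because late onset leaves fewer days in which to die.

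**4. Early onset.** Assume 25% of patients are susceptible, with onset hazard k. Take mean onset 4 days (k = 0.25) and L = 0.1.

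- Stay with complication: 1/0.35 + 10 = 12.9 days.
- Without: 75% non-susceptible with mean 10 days, plus 0.25 x 0.1/0.35 = 7.1% who leave before onset with mean 1/0.35 = 2.9 days. Weighted mean: (7.5 + 0.20)/0.821 = 9.4 days.
- Naive HR: 9.4/12.9 = 0.73 (simulated 0.72).

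Over mean onset of 1-4 days and mean stay of 10-15 days, simulation gave naive HR 0.72-0.93, 1.1-3.9 spurious extra days and 28-day OR 0.92-0.98.

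**The case against.** The strongest reply is that the article never says complications are coded yes/no. It names model families only. A parametric survival model can take a time-updated exposure, and the full protocol, the sub-study protocol and the case report forms are not shown. A reader might infer that the plan prescribes ever/never coding; the text does not support that, so the bias is conditional.

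Three further limits also stand:

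- **Not every complication is affected.** Those present at ICU admission carry no immortal time from day 0.
- **Not every mortality estimate is affected.** The odds ratio for death before discharge shows no bias under constant hazards. With changing hazards it could go either way.
- **It is not stated that death will be analysed as time-to-event.** It is collected as status at discharge and at 28 days, so the hazard-ratio figures matter only if a survival model is fitted to death.

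The reply does not dispose of the point. The section settles model families, adjustment and effect measures, and it deals with time at risk for incidence, yet has no counterpart for outcomes. A one-row-per-patient mixed model for 28-day death cannot respect onset time without a landmark or person-day structure. Length of stay is the hardest outcome to protect, because the stay itself creates the exposure.

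**Conclusion.** The point holds in conditional form. The plan relates ICU-onset complications to mortality and length of stay without tying exposure to onset. A standard ever/never fit of the named models would distort three results: the death hazard ratio, the length-of-stay association and, mainly for later-onset complications, the 28-day death odds ratio.

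Under constant onset and exit hazards and no true effect, the death hazard ratio falls to about 0.36-0.50 and the stay appears about 2.0-2.7 times longer. In the scenarios where the true hazard ratio was 2, the naive estimate fell below 1. With early onset the hazard ratio is about 0.72-0.93 and the 28-day odds ratio is close to null, so a reader should not conclude that the naive hazard ratio always lies below one half. These sizes illustrate assumed hazards; they do not predict this cohort's results. Nor do the documents support saying that all complications, or all mortality estimates, will be biased.

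**What to change.** Amend the Statistical Analysis Plan section as follows:

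1. Set ICU admission as the time origin.
2. Enter complications present at ICU admission as baseline exposures, separately from those with onset in ICU.
3. In the survival models, enter each ICU-onset complication as a time-dependent exposure: unexposed until onset, exposed afterwards.
4. For 28-day death, use a landmark analysis (complication status at fixed ICU days among patients still in ICU) or take the result from the time-dependent model.
5. Report length of stay as excess stay after onset from a multistate model, in place of an ever-versus-never comparison.

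The cost is wording and programming, with no new patients. Records without an onset date need a sensitivity analysis, and landmarking drops early exits. The authors should confirm that the case report forms hold onset dates, which the article text does not show.
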